**Weaning of MediPharm Labs MPL-001 Oil**

[figure not shown]

At visit 6, participants and their parents will be instructed on how to wean the investigational product starting from 0.8-0.6 mg/kg/day, incrementally decreasing the dose of administered study product over time (See Table 5) in weekly increments. If the adolescents and clinicians feel that there was an improvement in chronic headache, participants will be offered medical cannabis authorization to access a 1:25 THC:CBD product at the end of the study.

[figure not shown]

**Table: 5** The weaning schedule of the MediPharm Labs MPL-001 Oil at visit 6

| **Visit 6** | **Dose** | **Frequency** | **Duration** |
| --- | --- | --- | --- |
| Week 1 | 0.6-0.8 mg/kg/day | BID | 7 days |
| Week 2 | 0.4-0.6 mg/kg/day | BID | 7 days |
| Week 3 | 0.2-0.4 mg/kg/day | BID | 7 days |
| Week 4 | 0 mg/kg/day | BID | 7 days |
| *Visit 7: Assessment of ADR, electronic headache diary, blood samples, Score of questionnaires, out of pocket expenditures, quality of life score | | | |

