## Schema

[figure not shown]

**Figure 1:** A flow chart of participant enrollment, treatment with CBD-Enriched CHE, monitoring and weaning

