# STUDY DESIGN

## Overall Design

This is multicenter phase 2, single group assignment, open-label dose-escalation, pharmacokinetic trial. A traditional 3+3 dose-finding design was not practical as all participants would not receive the lowest cannabinoid dose and the recommended “start low and go slow” approach to titration. The trial will be conducted across three centres in Canada and was designed in collaboration with youth from the KidsCAN Young Persons’ Advisory Group (YPAG) and the Solutions for Kids in Pain (SKIP) network. The Canadian Childhood Cannabinoid Clinical Trials Parent Advisory Committee provided insight on the outcome measurement tools and the consent form. Three youth advisors with chronic migraines have been involved throughout the study design process and will advise on recruitment strategies, reporting and dissemination as steering committee members. The youth engagement plan, findings and evaluation are described elsewhere (*publication under review)*. The research team held three virtual meetings with youth advisors to discuss which outcomes are important to youth, and decided on data collection methods and tools. The research team also co-designed the recruitment materials, including consent forms, with youth advisors. The PI will send safety reports annually to Health Canada as a Clinical Trial Notification to strengthen the evidence base of product specific cannabis data. The study will consist of three different phases: baseline (1 month), followed by escalating treatments monthly. Participants will wean in the same dosing increments over 4 weeks and will complete a pre and post study questionnaire.

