**Treatment Phase (visit 2 to visit 5)**

Before visit 2 (start of the second month) the study participants will receive CBD-enriched CHE (MPL-001) and a dosing calendar shipped to their homes before visit 2. Participants will be instructed to administer it at a dose of 0.2-0.4 mg/kg of CBD per day divided into two doses (25% in the morning and 75% in the afternoon after school). Participant-specific dose will be prescribed by site investigator. Participants will be asked to administer CHE with food.

Participants will complete monthly study visits and receive a one monthly supply of MPL-001. They will be instructed on how many drops to administer daily for the following one-month period. Participants will be asked to administer the intervention for the next month at escalating doses of 0.4-0.6 mg/kg/day then 0.6-0.8 mg/kg/day at the visit 4, and finally 0.8-1.0 mg/kg/day at visit 5. Blood samples will be drawn each month to measure the plasma concentration of CBD, THC, and its metabolites before increasing the dose, pregnancy test and liver and renal safety lab test. For all the follow-up visits, participants will be asked to provide information about PedsQL ™ Family Impact Module assessment and perception of improvement, self-directed goal attainment scaling.

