**Weaning Phase (from visit 6 to visit 7)**

After the baseline phase (one month) and the treatment phase (four months), participants will start the weaning schedule, which comprises incrementally reducing the dose leading to complete discontinuation of the study product. The intervention dose will be decreased in 0.2mg/kg increments every week. The intervention will be discontinued by visit 7. If the parents, adolescents, and healthcare providers feel an improvement in chronic headache, participants will be offered a medical cannabis authorization at the end of the study.

All participants and their caregivers will be invited to complete a post-study interview (telephone) about their experiences in the trial to inform future research. Questions will be asked around their overall impression of the trial, perceived risks, benefits, how it changed during the trial, outcome importance for future studies, challenges they encountered, and how we can improve our trial. More specific questions will also be asked on the usability and usefulness of the consent form, recruiting materials, outcomes measured and the daily headache collection tool.

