After one month of the intervention, the participants will receive new supply/supplies of the investigational product from CHRIM during visits 3 through 5 (See table 4). The 6^th^ month will include a weekly weaning period where the dose is reduced each week at the same rate as the dose escalation (0.2mg/kg/day) (See table 5). To maintain the accuracy and consistency in the dosing regimen of the study participants across all the study centres, the mid-point of the dose range will be selected to calculate the desired dose based upon the weight of the participants. Participants will be weighed on site at each study visit. However, the dose calculation will be based on the weight taken at baseline. The final dose will be calculated by rounding off the nearest 1 mg of CBD. As an exemplary 24 kg, (0.3mg/kg/day) adolescent will receive a dose of 7 mg/day. This will help achieve improved efficacy, precision in dosing and ease the administration of the MPL-001 (CBD:THC 25:1) oil to the study participants.

**Table: 4** The single escalating dose of the MediPharm Labs MPL-001 Oil from visit 2 to visit 5

| **Visit** | **Dose** | **Frequency** | **Duration** |
| --- | --- | --- | --- |
| Visit 2 | 0.2-0.4 mg/kg/day | BID | 1 month |
| Visit 3 | 0.4-0.6 mg/kg/day | BID | 1 month |
| Visit 4 | 0.6-0.8 mg/kg/day | BID | 1 month |
| Visit 5 | 0.8-1 mg/kg/day | BID | 1 month |

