# STUDY INTERVENTION DISCONTINUATION AND PARTICIPANT DISCONTINUATION/WITHDRAWAL

## Dose limiting toxicity and Discontinuation of Study Intervention

Adverse events are categorized using the Common Terminology Criteria for Adverse Events (CTCAE version 5.0 dated 27 Nov 2017). If any of the following occur the participant will not move up to the next dose level (dose limiting toxicities):

1. Parental/youth report complaints of moderate mood elevation defined as exaggerated feelings of well-being which is disproportionate to the events and stimuli (Euphoria Grade 2)
2. Somnolence Grade 2 which includes moderate sedation (sleepiness and drowsiness) that limits instrumental activities of daily living
3. Cannabis-attributed diarrhea, Grade 2 or more defined as an increase of 4 - 6 stools per day over baseline; moderate increase in ostomy output compared to baseline; limiting instrumental activities of daily living
4. Unexplained tachycardia (w/out pain, fever, anemia etc.) requiring medical intervention
5. Unexplained hypotension requiring medical intervention
6. Non-infectious conjunctivitis Grade 2 defined as moderate decrease in visual acuity (best corrected visual acuity 20/40 and better or 3 lines or less decreased vision from known baseline) characterized by inflammation, swelling and redness to the conjunctiva of the eye.
7. Serious adverse events requiring hospitalization
8. Discretion of the participant, physician, or parents

Discontinuation from the study intervention does not mean interruption from the study, and remaining study procedures should be completed as indicated by the study protocol.

There will be no replacement of the study participants who were administered the investigational product, withdraw from the study, and lose follow-up (after signing an informed consent form). The main reason for the withdrawal of participants from the study will be noted in the participant's Case Record Form (CRF). The site investigator should contact the participants who fail to report during the follow-up visits which will be documented in the CRF.

Adverse events (AEs) and SAEs (Serious Adverse Events) will be reported according to Health Canada and Institutional regulations and reviewed by the data safety monitoring board (DSMB). The DSMB will hasten safety review if death is deemed related or potentially relevant to CBD-enriched CHE used in the study as the investigational product.

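### The visit 6 wean is printed with one starting dose, 0.6-0.8 mg/kg/day, which is a reduction only for participants who reached 0.8-1.0 mg/kg/day

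*Protocol*

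**What the plan says.** Four parts of the protocol bear on this.

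- **Weaning of MediPharm Labs MPL-001 Oil, and Table 5.** At visit 6 families are "instructed on how to wean the investigational product starting from 0.8-0.6 mg/kg/day, incrementally decreasing the dose of administered study product over time". Table 5 gives four weekly rows: 0.6-0.8, 0.4-0.6, 0.2-0.4 and 0 mg/kg/day. Neither the sentence nor the table depends on the level the participant has reached. The Schedule of Activities marks visit 6 as a wean and gives no dose.
- **General weaning rule.** The Weaning Phase paragraph says "The intervention dose will be decreased in 0.2mg/kg increments every week". Overall Design says "Participants will wean in the same dosing increments over 4 weeks". Dosing and Administration also sets a weekly cut of 0.2 mg/kg/day and refers the reader to Table 5.
- **Dose limiting toxicity and Discontinuation of Study Intervention.** "If any of the following occur the participant will not move up to the next dose level (dose limiting toxicities". The list covers specified toxicities, serious events with hospitalization, and the discretion of the participant, physician or parents. Coming off the product is dealt with separately in the same section.
- **Who sets the dose.** In the Treatment Phase paragraph, "Participant-specific dose will be prescribed by site investigator". Dosing and Administration adds that each shipment carries an individual dosing calendar.

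**The concern.** The protocol itself creates a group that can arrive at visit 6 below the top level: participants held for a listed toxicity or by choice. The printed wean takes no account of them. Read literally, it would start some of them on a dose higher than the one they are taking, in a month meant for tapering. Those held for a dose-limiting toxicity are the ones for whom this matters most.

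What is at stake is the clarity of a dosing instruction for adolescents. For a held participant the visit 6 instruction and the weekly reduction rule cannot both be followed, and nothing in the readable text says which gives way.

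**Working it through.** **Inputs**

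- Dose levels from Table 4, numbered here 1 to 4 for the doses given at visits 2 to 5: 0.2-0.4, 0.4-0.6, 0.6-0.8 and 0.8-1.0 mg/kg/day.
- Dosing and Administration calculates each dose at the mid-point of its range and rounds to the nearest 1 mg of CBD. The mid-points are 0.3, 0.5, 0.7 and 0.9 mg/kg/day.
- Table 5 at the same mid-points: 0.7, 0.5, 0.3 and 0 mg/kg/day.
- Stated weekly reduction: 0.2 mg/kg/day.

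**Reproducing the protocol's own figures**

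- From level 4: 0.9 - 0.2 = 0.7, then 0.7 - 0.2 = 0.5, then 0.5 - 0.2 = 0.3. These are weeks 1 to 3 of Table 5, so the table is built for someone leaving level 4.
- The rounding example is "As an exemplary 24 kg, (0.3mg/kg/day) adolescent will receive a dose of 7 mg/day". Check: 0.3 x 24 = 7.2, which rounds to 7.

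**Week 1 change if Table 5 is applied as printed**

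Change = 0.7 - current mid-point. The last column uses the protocol's 24 kg example: 0.3 x 24 = 7.2, 0.5 x 24 = 12, 0.7 x 24 = 16.8 and 0.9 x 24 = 21.6, rounded to 7, 12, 17 and 22 mg.

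| Level at visit 6 | Current dose (mg/kg/day) | Printed week 1 (mg/kg/day) | Change (mg/kg/day) | At 24 kg (mg/day) |
| --- | --- | --- | --- | --- |
| 1 | 0.3 | 0.7 | +0.4 (+133%) | 7 to 17 (+10) |
| 2 | 0.5 | 0.7 | +0.2 (+40%) | 12 to 17 (+5) |
| 3 | 0.7 | 0.7 | 0 | 17 to 17 (0) |
| 4 | 0.9 | 0.7 | -0.2 (-22%) | 22 to 17 (-5) |

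Only level 4 receives the stated reduction. At levels 1 and 2 the printed start is also a move to a higher level.

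**At other body weights**

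The protocol gives no expected weight. Assuming 40 to 70 kg, level 1 would go from 12-21 mg/day to 28-49 mg/day (0.3 and 0.7 times weight), and level 2 from 20-35 mg/day to 28-49 mg/day (0.5 and 0.7 times weight).

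**The case against.** The best defence is that Table 5 is simply the planned path. Table 4 is just as unconditional, giving one dose per visit, yet everyone would read it subject to the toxicity rule. Table 5 mirrors it on the way down, and the visit 6 sentence itself speaks of decreasing the dose. An increase at visit 6 would contradict that sentence as well as the toxicity rule. This is a plausible account of the intention, and with investigator prescribing and individual calendars it makes real up-dosing unlikely. But no readable text says that Table 5 assumes level 4 was reached, and neither the prescribing rule nor the calendar says what a held participant should receive.

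Two further objections limit the point without removing it. The toxicity section does not say outright that a held participant stays on the current dose. That is the natural meaning of not moving up, since stopping the product is treated separately. Also, two figures beside the weaning text are not shown, nor is the schema captioned "A flow chart of participant enrollment, treatment with CBD-Enriched CHE, monitoring and weaning". They may carry more detail, so the point concerns the readable text only.

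A reader might infer more than the protocol supports:

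- **That the weekly rule leaves level 1 at an unplanned 0.1 mg/kg/day.** Literal steps of 0.2 from level 4 also reach 0.1 in week 4 (0.9, 0.7, 0.5, 0.3, 0.1), where Table 5 prints 0. That mismatch is not specific to held participants, and Table 5 suggests stepping down by dose level.
- **That a four-week wean in steps of 0.2 cannot fit the lower doses.** The Weaning Phase paragraph requires only that the product be stopped by visit 7, so a shorter wean is allowed.
- **That held participants will in fact be re-escalated, or that the adverse event results are compromised.** The wording, the prescribing arrangement and the bar on moving up all point against re-escalation, and nothing shows an effect on the primary endpoint.

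**Conclusion.** Wrong as written, and minor. In the readable text the visit 6 instruction and Table 5 give every participant a wean starting at 0.6-0.8 mg/kg/day, which is a reduction only from 0.8-1.0 mg/kg/day. At mid-points the printed week 1 is +0.4 mg/kg/day at level 1, +0.2 at level 2 and 0 at level 3. All three contradict the weekly 0.2 mg/kg reduction, and the first two also contradict the bar on moving up.

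This rests on two assumptions: that a held participant continues at the held level to visit 6, and that the figures not shown do not already give level-specific schedules. The protocol does not say how many of the 20 participants might be held, so the number affected cannot be stated.

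**What to change.** Add one sentence to the visit 6 text: weaning starts at the first Table 5 row below the level the participant is actually taking and follows the remaining rows weekly to zero. Add a note under Table 5 that it applies as printed to participants at 0.8-1.0 mg/kg/day.

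Weekly mid-point doses (mg/kg/day) would then be:

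- level 4: 0.7, 0.5, 0.3, 0 (unchanged)
- level 3: 0.5, 0.3, 0
- level 2: 0.3, 0
- level 1: 0

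Every step is a decrease and only existing dose levels are used. No step exceeds the last one already in Table 5 (0.3 to 0). The sponsor's clinicians should confirm the steps, in particular the direct stop from level 1.

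The cost is one sentence, one table note and a line in the dosing calendar template. No visits or procedures are added.

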## Preparation/Handling/Storage/Accountability

### Acquisition and accountability

Our study ensures strict compliance with Health Canada's requirements for conducting the clinical research study involving the cannabis product. Special care is taken to assure accountability concerning the investigational product dispensed and utilized by the study participant. Investigational product will be shipped to participants in batches and accountability documented on the dosing calendar will be reviewed with the study team at each monthly visit. The MediPharm Labs MPL-001 Oil will be shipped, stored, dispensed, destroyed and documented according to the trial specific site SOPs.

### Formulation, Appearance, Packaging, and Labeling

MediPharm Labs MPL-001 Oil is packaged in a pharmaceutical-grade amber glass bottle with a 1mL syringe for consistent dosing. Study dosage and protocol number will be marked on the bottles.

### Product Storage and Stability

The study product is packaged in 30 mL amber bottles with child-resistant caps. The bottles must be stored at room temperature (15 to 25 °C).

The study participants will be instructed to cap the bottle after use and keep it away from direct sunlight.

### Preparation

MediPharm Labs MPL-001 Oil will be made ready to be dispensed as oil bottles. The study team at each site will be given rigorous training to prevent any dispensing errors.

## Measures to Minimize Bias: Randomization and Blinding

This is a non-randomized, open-label tolerability study.

## Study Intervention Compliance

The study participants will be instructed to maintain the daily electronic diaries, which will help monitor the participant’s compliance. During each follow-up visit, the study team will review the participant’s dosing calendar. The study participants will be provided with return packaging and labels to return the unused extract or empty bottles to the study central pharmacy where it will be destroyed as per local SOPs. However, we will also draw the blood sample from the participants to measure the plasma concentration of CBD, THC, and their metabolites during all the follow-up visits starting from visit 2.

## Concomitant Therapy

For this protocol, prescription medication is defined as a medication prescribed only by a duly authorized/licensed clinician. Medications and other concomitant therapies reported in the Case Report Form (CRF) will include all concomitant prescription medications, over-the-counter medications, and supplements including nutraceuticals such as magnesium. Therapies including physical and psychological will also be recorded in the daily diary.

The concomitant medications will be recorded from (Baseline phase) visit 1 until the last study visit. The participant/caregiver will be asked to record the frequency dosage and duration of concomitant medications, all use of rescue medications and will be asked to present the list during each follow-up visit.

**Prohibited medications:**

All opioids including tramadol, antipsychotics, antimanic meds, barbiturates, benzodiazepines, muscle relaxants, or sedatives should be avoided by participants during the entire study duration.

### Rescue Medicine

The participants will be asked to keep track of all medications during the study period. It will help to understand the influence of the study intervention, including any medicines provided as rescue medication should a visit to the emergency department be required.

# STUDY INTERVENTION DISCONTINUATION AND PARTICIPANT DISCONTINUATION/WITHDRAWAL

## Dose limiting toxicity and Discontinuation of Study Intervention

Adverse events are categorized using the Common Terminology Criteria for Adverse Events (CTCAE version 5.0 dated 27 Nov 2017). If any of the following occur the participant will not move up to the next dose level (dose limiting toxicities):

1. Parental/youth report complaints of moderate mood elevation defined as exaggerated feelings of well-being which is disproportionate to the events and stimuli (Euphoria Grade 2)
2. Somnolence Grade 2 which includes moderate sedation (sleepiness and drowsiness) that limits instrumental activities of daily living
3. Cannabis-attributed diarrhea, Grade 2 or more defined as an increase of 4 - 6 stools per day over baseline; moderate increase in ostomy output compared to baseline; limiting instrumental activities of daily living
4. Unexplained tachycardia (w/out pain, fever, anemia etc.) requiring medical intervention
5. Unexplained hypotension requiring medical intervention
6. Non-infectious conjunctivitis Grade 2 defined as moderate decrease in visual acuity (best corrected visual acuity 20/40 and better or 3 lines or less decreased vision from known baseline) characterized by inflammation, swelling and redness to the conjunctiva of the eye.
7. Serious adverse events requiring hospitalization
8. Discretion of the participant, physician, or parents

Discontinuation from the study intervention does not mean interruption from the study, and remaining study procedures should be completed as indicated by the study protocol.

There will be no replacement of the study participants who were administered the investigational product, withdraw from the study, and lose follow-up (after signing an informed consent form). The main reason for the withdrawal of participants from the study will be noted in the participant's Case Record Form (CRF). The site investigator should contact the participants who fail to report during the follow-up visits which will be documented in the CRF.

Adverse events (AEs) and SAEs (Serious Adverse Events) will be reported according to Health Canada and Institutional regulations and reviewed by the data safety monitoring board (DSMB). The DSMB will hasten safety review if death is deemed related or potentially relevant to CBD-enriched CHE used in the study as the investigational product.

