## Participant Discontinuation/Withdrawal from the Study

Participants are free to withdraw from the study at any time. QI may discontinue or withdraw a participant from the study for the following reasons:

- The study participants suffer treatment-related intolerable adverse effects
- If the participant's headache gets worse
- The participant becomes pregnant
- The participant is unable to attend the study site for the follow-up visits
- The study participant does not comply with the prescribed regimen of the investigational drug
- The study terminated at a particular site either by site qualified investigator, principal investigator or due to any other reasons such as administrative
- If the participant meets an exclusion criterion (either newly developed or not previously recognized) that precludes further study participation

The reason for participant discontinuation or withdrawal from the study will be recorded on the CRF. Participants will be given the option to only withdraw from the study intervention, these participants will continue to be followed up till the end of study (visit 7) with the other assessments listed in SOA.

Participants who sign the informed consent form and are enrolled but do not receive the study intervention may be replaced. Study participants who sign the informed consent form and are enrolled receiving the study intervention and subsequently withdraw/discontinue will not be replaced.

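### The mandatory no-escalation list names Grade 2 alone for euphoria, somnolence and conjunctivitis, so read literally it holds the dose for a moderate event but not always for a worse one

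*Protocol*

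**What the plan says.** Section 8.1 (Dose limiting toxicity and Discontinuation of Study Intervention) grades events by CTCAE version 5.0 and sets a mandatory rule: "If any of the following occur the participant will not move up to the next dose level (dose limiting toxicities". Eight items follow, and four of them carry a grade.

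- Item 1 (euphoria) is worded as moderate mood elevation "which is disproportionate to the events and stimuli (Euphoria Grade 2".
- Item 2 reads "Somnolence Grade 2 which includes moderate sedation (sleepiness and drowsiness) that limits instrumental activities of daily living".
- Item 3 reads "Cannabis-attributed diarrhea, Grade 2 or more defined as an increase of 4 - 6 stools per day over baseline", followed by limbs on ostomy output and on limited instrumental activities.
- Item 6 reads "Non-infectious conjunctivitis Grade 2 defined as moderate decrease in visual acuity (best corrected visual acuity 20/40 and better or 3 lines or less", measured against the known baseline.

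Items 4 and 5 (unexplained tachycardia and hypotension) are defined by the need for medical intervention and carry no grade. Item 7 covers serious events that require hospitalization. Item 8 is "Discretion of the participant, physician, or parents".

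Outside the list, the section on participant withdrawal (8.2) says "QI may discontinue or withdraw a participant from the study for the following reasons", and intolerable treatment-related effects are among those reasons. Under the Treatment Phase in Overall Design, "Participant-specific dose will be prescribed by site investigator".

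**The concern.** One of the four graded items extends above Grade 2 and three do not. Because the contrast sits inside a single list, a site could take it as deliberate. If so, the rule behaves perversely: moderate euphoria or moderate visual loss blocks the next dose step, while a more severe form of the same event, short of hospitalization, does not.

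What is at stake is individual safety and consistency between sites. This is a tolerability study in participants aged 14 to 17, with planned monthly increases of a product that contains THC, run at three centres. A mandatory rule exists so that the same event leads to the same dose decision everywhere. With this wording, a site that reads Grade 2 literally and a site that reads it as a minimum could treat the same severe, non-hospitalized event differently at the next step.

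**Working it through.** The check is a reading of the text, item by item, and depends on no alpha, power or effect size. The protocol states no figure on this point to reproduce.

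**Does each graded item reach events worse than Grade 2?**

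| Item | Grade named | Descriptor | Reaches worse than Grade 2? |
| --- | --- | --- | --- |
| 1 Euphoria | 2 | Moderate mood elevation | No. Severe elevation is neither Grade 2 nor moderate. |
| 2 Somnolence | 2 | Moderate sedation that limits instrumental activities | Ambiguous. Worse somnolence also limits those activities. |
| 3 Diarrhea | 2 or more | 4 to 6 extra stools per day, or other limbs | Yes by its label and its activity limb. Only the stool count stops short. |
| 6 Conjunctivitis | 2 | Acuity 20/40 and better, or loss of 3 lines or less | No, when both limits are exceeded. |

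Items that name Grade 2 without extension: 1, 2 and 6, so 3 of 4. Items with the extension: item 3, so 1 of 4. The clear cases are items 1 and 6.

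**Where do the numeric descriptors stop?**

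- Item 3: the first whole value beyond the range is 6 + 1 = 7 extra stools per day. From there the count conflicts with the item's own label.
- Item 6: the two limbs are joined by *or*, so exceeding one limit is not enough to escape. An event falls outside only if more than 3 lines are lost (3 + 1 = 4 or more, in whole lines) **and** acuity is worse than 20/40.

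**Does other text supply the missing words?**

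- Item 7 reaches only serious events that require hospitalization.
- Item 8 is in the mandatory list, but it operates only if someone chooses to invoke it.
- Section 8.2 permits withdrawal and does not require it.
- The Treatment Phase text leaves the prescribed dose to the site investigator.
- Adverse Event Reporting (9.3.5) requires severe related events to be entered within 24 hours and assessed, but attaches no dose consequence.
- Section 8.1 hastens the data safety monitoring board's review only for a death that is related or potentially relevant to the product.

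None of these extends the list above Grade 2.

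**How often is the rule consulted?** Doses rise at visits 3, 4 and 5 (to 0.4-0.6, 0.6-0.8 and 0.8-1.0 mg/kg/day). With 20 participants, that is at most 20 × 3 = 60 step-up decisions. This is the number of times the list is applied, not the number of participants harmed. The risk section gives drowsiness at 23-25%, the highest range it lists, but without grades, so no expected count can be derived.

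**The case against.** The strongest reply is that the gap is unlikely to matter in practice.

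- **Item 8 is part of the mandatory list.** Once the participant, a parent or the physician objects, the hold applies. For escalation to go ahead, all of them would have to accept it after severe euphoria or marked visual loss, at a site that already holds for the moderate form. This stands as a reason to think harm improbable. It does not make the toxicity rule itself mandatory above Grade 2.
- **There are further safeguards.** The primary endpoint has adverse events evaluated monthly before each escalation, adverse-event review is scheduled at visits 2 to 7, and the data safety monitoring board can recommend changing or stopping the trial. These lower the chance of an inadvertent step-up, but none of them says what must happen to the dose.
- **Only two items are clear.** This stands. Item 3's label governs, and item 2's wording can be read to include worse somnolence.
- **Many severe events pass through Grade 2.** The section on time period and follow-up (9.3.4) requires changes in severity to be documented, so an event recorded at Grade 2 while worsening or resolving has met the item. This also stands, and it narrows the gap to events recorded only above Grade 2.
- **It is a wording matter and leaves the endpoint alone.** Agreed. All adverse events are recorded, graded and summarized whatever the list says.

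**Conclusion.** The concern holds, as a minor one. Items 1 and 6 do not, as written, hold the dose for a non-hospitalized event worse than Grade 2. Item 2 can be read either way. The stool count in item 3 is inconsistent with its own label but opens no real gap. The conclusion rests on a literal reading of section 8.1 and on the absence of any text elsewhere that extends the list.

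The probable intent is Grade 2 as a minimum, and a sensible investigator would probably hold the dose. That is a reason to write the intent down, because this is the participant-level escalation rule and three sites must apply it alike. The number of participants affected cannot be estimated from the protocol. The descriptive adverse-event analysis is not compromised.

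This is not a detail to be left to a statistical analysis plan: escalation criteria belong in the protocol, and the list is already there.

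**What to change.** Amend section 8.1 as follows.

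- Items 1, 2 and 6: replace the bare grade with *Grade 2 or higher*. In item 1, also change the descriptor so that it covers moderate or greater mood elevation.
- Item 3: set the stool criterion at an increase of 4 or more per day over baseline.
- Item 6: remove the upper limit on visual loss, so that a loss beyond 3 lines or acuity worse than 20/40 also counts. Once the grade reads *Grade 2 or higher* this is partly redundant, but it stops the descriptor from contradicting the grade.

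The cost is amendment wording only, with no added visits, procedures or participants. The one downside is that a few participants may be held at a dose level, which is what the rule is for.
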